**Reach**			
	Number of participants who did not consent to participate and number not included in the trial	Monitoring (registers)	
	Reasons	Interviews and registers	
	Number lost to follow-up	Monitoring (baseline to month 6)	
**Efficacy**			
	Proportion of participants who have ≥1 session per week	Monitoring (registers and journals)	
	Proportion with participation of ≥75% of the sessions	Monitoring (registers and journals)	
	Reason for adherence and nonadherence	Interviews	
**Adoption**			
	Acceptability	Questionnaires (weeks 12, 24, and 48) and interviews	
	Satisfaction	Interviews	
**Implementation (fidelity)**			
	Number of modifications implemented	Monitoring and observations	
**Maintenance (phase 2)**			
	Proportion of participants with participation of ≥75% of sessions	Monitoring (≥6 months)	
	Proportion of participants with decreasing participation	Monitoring (≥6 months)	
	Proportion of participants having ≥1 session per week	Monitoring (≥6 months)	
	Reasons	Interviews	

The acceptability of the PA program will be assessed before and during implementation using the theoretical framework of acceptability [55], which encompasses the following constructs: affective attitude, burden, perceived effectiveness, ethicality, intervention coherence, opportunity costs, and self-efficacy.

The implementation outcomes and determinants will be measured using quantitative methods (process indicators and questionnaires) along with qualitative methods (semistructured interviews with participants and observations). Both approaches will be implemented concurrently with systematic triangulation of data as the project progresses.

### Evaluations and Data Collection

Data on the intervention’s efficacy and its implementation will be collected at multiple time points during the study to address the 2 main objectives of this research.

#### Initial (Baseline) Evaluation

This evaluation follows the International Classification of Functioning, Disability, and Health (ICF) framework [56], chosen for its holistic approach to health, encompassing physical, functional, and social dimensions. It provides information on participants’ physical capacities (strength, balance, and endurance), functional limitations, and social participation. In addition, cardiometabolic risk will be assessed via clinical (anthropometric characteristics and blood pressure) and biological (fasting glucose, glycated hemoglobin, cholesterol levels, and urinary branched-chain amino acid detection) evaluations. Urinary branched-chain amino acid is a screening test for insulin resistance, and elevated fasting glucose or glycated hemoglobin indicates impaired glucose metabolism and type 2 diabetes mellitus. Obesity, type 2 diabetes, insulin resistance, high blood pressure, and dyslipidemia are frequent conditions among people aging with HIV; these conditions are associated with major health challenges and can be effectively prevented through PA. Finally, depressive symptoms, dietary quality, alcohol consumption, and usual PA levels will be evaluated using validated questionnaires. The list of the evaluations performed is presented in Table 2, and a description of the physical tests is provided in Multimedia Appendix 2.

**Table 2 table2:** Summary of the evaluations performed (a detailed description of the tests is provided in Multimedia Appendix 2).

	Initial	Week 12	Week 24	Week 48
Clinical examination	✓		✓	✓
Heart rate, blood pressure, height, weight, body composition	✓		✓	✓
Sociodemographic characteristics and medical history	✓			
Diet quality questionnaire				
Functional test: 6-minute step-up test, grip strength measurement, gait speed test, stand-up test	✓		✓	✓
Balance tests (Y balance test, tandem, semitandem)	✓		✓	✓
Glycated hemoglobin, fasting blood glucose, cholesterol LDL^a^ and HDL^b^, triglyceride levels	✓			✓
IDIR^c^	✓		✓	✓
Neurocognitive evaluation (Neuroscreen)	✓			✓
Self-reported PA^d^ (GPAQ^e^ or IPAQ^f^)	✓		✓	✓
Social participation and activity limitation: IADL^g^, WHODAS-2^h^, HDQ^i^	✓		✓	✓
Quality of life (WHOQoL^j^-short)	✓		✓	✓
Alcohol consumption (AUDIT^k^)	✓			
Depression (PHQ-9^l^)	✓		✓	✓
Satisfaction with PA (questionnaire)		✓	✓	✓
Acceptability of the PA program		✓	✓	✓

^a^LDL: low-density lipoprotein (cholesterol).

^b^HDL: high-density lipoprotein (cholesterol).

^c^IDIR: urinary branched-chain amino acid measurement to detect insulin resistance.

^d^PA: physical activity.

^e^GPAQ: Global Physical Activity Questionnaire.

^f^IPAQ: International Physical Activity Questionnaire.

^g^IADL: Instrumental Activities of Daily Living.

^h^WHODAS-2: World Health Organization Disability Assessment Schedule-2.

^i^HDQ: HIV Disability Questionnaire.

^j^WHOQoL: World Health Organization Quality of Life.

^k^AUDIT: Alcohol Use Disorders Test.

^l^PHQ-9: Patient Health Questionnaire 9.

#### Follow-Up Visit (Week 12)

The aim of this visit is to identify potential challenges faced by participants in the intervention groups, particularly those in the home-based group. It will involve a structured interview with the coach to discuss the training experiences and potential problems encountered, and questionnaires on self-reported PA (Internation Physical Activity Questionnaire), satisfaction with PA, and acceptability of the intervention. The interviews will explore barriers to adherence, perceptions of exercise intensity, and suggestions for program improvement. The major issues identified will lead to tailored adjustments, which will be documented and monitored for their effects.

Some participants will also have semistructured in-depth interviews with a social scientist to delve deeper into their experiences during the initial months of the intervention.

#### Intervention (Week 24) and Maintenance (Week 48) Evaluation Visits

These visits will provide data for assessing the primary and secondary effectiveness outcomes (Table 2). The same evaluations as for the baseline will be performed alongside questionnaires on satisfaction, acceptability, and quality of life. In addition, in-depth semistructured interviews will be conducted with a subset of participants.

#### Data Management

Data will be collected on paper forms before being entered into a web application designed for this study. It includes an application server and database servers hosted at the PAC-CI program in Ivory Coast with regular backup on a second server located in another site and secure access via https, passwords, and multiple firewalls. The data entered into the database are monitored with consistency checks. In addition, a monitoring of the data collected is performed by the clinical research assistant according to a monitoring plan.

### Statistical Analysis

#### Sample Size

In a previous study, participants aged 50 years or older with HIV who reported high PA presented an improvement of approximately 10% in performance compared with those with low activity in the 6MWT (422 meters versus 380 meters) or the 6MST test (115 steps vs 105 steps) [38]. This difference is consistent with an estimated minimal clinically important difference of about 40 meters reported in other studies on older people or people with chronic disease [57,58], which translates into a difference of approximately 10 steps. Using these results, 50 participants per group will ensure 80% power to detect a significant difference between the intervention and control groups, assuming a type I error rate of 0.025 (adjusted for multiple comparisons regarding the primary end point). To accommodate attrition, each planned group size was increased by 20%, resulting in a total planned sample size of 180 participants. Importantly, this pilot study is powered to compare both intervention arms with the control arm but not to test for noninferiority between the exploratory and reference arms.

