### Randomization and Blinding

The participants will be randomized using a computer-generated randomization list in a 1:1:1 ratio into one of three arms. Randomization will use fixed-size blocks and be stratified by study site. An independent team, not involved in intervention delivery, recruitment, or participant assessment, will generate and keep the randomization sequences. The arm allocation will be provided to investigators through a web application. An alternative procedure has been prepared in case of difficulties with the internet connection. Because of the nature of the intervention, participants and coaches will be aware of the arm allocated. However, the investigators responsible for the outcome evaluation are not involved in the intervention delivery and will remain blinded to the group assignments.

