#### Data Analysis

Primary analyses will use the intention-to-treat approach, considering all included participants in their initial groups and using all data, regardless of the intervention participation level. If protocol deviations are frequent, a per-protocol analysis will be conducted, with a focus on participants who followed the intervention.

The primary outcome analysis will compare scores between groups with modified covariance analysis (ANCOVA), using a linear regression model to analyze postintervention results in relation to the intervention group while accounting for baseline values, age, and sex. Robust linear regression will be used if necessary. A parallel gatekeeping procedure with the following four families of end points will be used to control the type I error risk for secondary end points: (1) the primary family includes the end points related to physical capacity (6MST, strength, and 30-second stand-up test), (2) comorbidities (high blood pressure, high fasting glycemia, obesity, and insulin resistance), (3) disability (HIV Disability Questionnaire scores), (4) mental health (quality of life and Personal Health Questionnaire 9 scores). End points of comorbidities, disability, and mental health families will be analyzed only if at least one primary end point is significant (with the Hommel method used to control for type I error). Secondary end points will be analyzed using the same approach with the ANCOVA model. Exploratory analyses will analyze repeated data using mixed-effects linear models, and Generalized Additive Mixed Model will be used to model nonlinear relationships. Missing data will be described and imputed using multiple imputations by chained equations, assuming that they are randomly missing, with estimates obtained via Rubin’s method.

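### The only rule stated for the two 6MST comparisons with control is an equal 0.025 split; this is valid, but Holm would give more power at the same 5% familywise level

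*Protocol article*

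**What the plan says.** The Sample Size section plans for two primary contrasts, each intervention arm against control, on an effect of about 10 steps ("or the 6MST test (115 steps vs 105 steps"). The error rate used for each contrast is given by the words "assuming a type I error rate of 0.025 (adjusted for multiple comparisons regarding the primary end point". At that level, the section claims, "50 participants per group will ensure 80% power to detect a significant difference between the intervention and control groups". It adds that the trial is "powered to compare both intervention arms with the control arm". Allocation uses a "computer-generated randomization list in a 1:1:1 ratio into one of three arms" (Randomization and Blinding).

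The Data Analysis section describes a covariance-adjusted linear model for the primary outcome and gives no decision rule for the two arms. It then sets out a parallel gatekeeping scheme, introduced as type I error control for the secondary end points, "with the Hommel method used to control for type I error". The first family contains the 6MST, strength and the 30-second stand-up test. All the families are lists of end points; arm contrasts are not mentioned.

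**The concern.** With two contrasts on one end point, 0.025 is 0.05 divided by two. If the final tests keep that split, the analysis ignores a simple fact: once one contrast has been rejected at 0.025, the other may be tested at 0.05 without exceeding 5% familywise error. A stepwise test rejects everything the fixed split rejects, and sometimes more.

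The trial wants an answer on both delivery strategies, and the Discussion presents the home-based arm as the one stakeholders can more easily adopt. The Results section reports that all participants are randomized, so the sample size is settled. The choice of test is one of the few remaining ways to protect power.

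**Working it through.** **Inputs.** From Sample Size: 50 evaluable per arm, 80% power, type I error 0.025 per contrast, difference of about 10 steps. From Randomization and Blinding: 1:1:1 allocation. Sidedness is not stated; two-sided is assumed.

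**The plan's own figure.** The article gives no standard deviation for the 6MST, so 50 per arm can only be back-solved:
- Noncentrality needed: z(0.9875) + z(0.80) = 2.241 + 0.842 = 3.083.
- Standardised effect: 3.083 / √(50/2) = 3.083 / 5 = 0.617.
- Implied SD: 10 / 0.617 = 16.2 steps.
- Total: 50 × 1.2 × 3 = 180, as stated.

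The comparison of procedures below uses only the noncentrality of 3.083, so it does not depend on the SD.

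**Correlation.** Each contrast has variance 2σ²/n, and the shared control mean contributes covariance σ²/n. The correlation is therefore 0.5.

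**Rules compared (two-sided p values).**
- Fixed split: reject a contrast if its p ≤ 0.025.
- Holm: compare the smaller p with 0.025; if it is rejected, compare the other with 0.05.
- Hommel (the same as Hochberg for two tests): reject both if both p ≤ 0.05; otherwise reject a contrast only if its p ≤ 0.025.

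**Both arms effective as planned** (bivariate normal probabilities; simulation agrees to within 0.1 point):

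| Rule | Each arm | Both arms | At least one |
|---|---|---|---|
| Fixed 0.025 | 80.0% | 68.7% | 91.3% |
| Holm | 84.6% | 77.8% | 91.3% |
| Hommel | 85.3% | 78.6% | 92.1% |

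Consistency check for equal arms, where power per arm = (both + at least one) / 2. Fixed: (68.7 + 91.3) / 2 = 80.0. Holm: (77.8 + 91.3) / 2 = 84.6.

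**Home arm at 70% of the planned effect** (illustrative assumption). Home-arm power: 46.7% fixed, 55.9% Holm, 56.7% Hommel.

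**Only one arm effective.** Power for that arm: 80.0% fixed, 80.2% Holm, 80.3% Hommel. False rejection of the null arm: 2.5%, 4.2% and 4.4%.

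**Neither arm effective.** Any false rejection: 4.7% fixed, 4.7% Holm, 4.8% Hommel. All stay below 5%.

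**Effect on the gate.** Holm leaves the chance of at least one 6MST rejection unchanged at 91.3%. Exactly one contrast is rejected in 91.3 − 77.8 = 13.5% by the rounded figures (13.4% unrounded).

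**The case against.** **The 0.025 is only a planning level.** It appears as a sample-size assumption, and nowhere does the article say that the final 6MST tests will be judged at a fixed 0.025. Sizing at half of alpha and then testing stepwise is ordinary, conservative practice. This stands: a reader might infer that the plan has committed itself to the less powerful test, and the text does not go that far. What remains is that no other rule for these contrasts is given.

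**Hommel may already cover them.** The 6MST is in the gatekeeping scheme's first family, and testing it in a three-arm trial means testing its contrasts. But that family spans three end points and does not mention arms. Hommel across three end points is a different rule from 0.025 for each of two contrasts. On this reading too, the rule needs stating.

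**The 69% looks like a broken promise.** A reader might set it against the claim that "this pilot study is powered to compare both intervention arms with the control arm". The natural meaning of that claim is 80% for each comparison. The article promises nothing about succeeding on both, so there is no contradiction.

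**The gain is a best case.** It needs both arms to have some effect, as the plan assumes. It also shrinks if baseline adjustment already lifts power. If the sizing ignored that adjustment (an assumption), a baseline correlation of 0.5, 0.6 or 0.7 gives per-arm power of 90.6%, 94.7% or 98.1% with the fixed split and 93.6%, 96.6% or 98.9% with Holm. The gain is then about 3, 2 or 1 points.

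**It is not wholly free inside a gatekeeping scheme.** Holm at the full 0.05 leaves no alpha to pass to later families when only one contrast is rejected, whereas a fixed split would pass on 0.025. This stands and shapes the fix, but does not defeat it: the gate opens on the 6MST just as often.

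**Conclusion.** The point holds as a cheap improvement. The equal split controls type I error and nothing in it is wrong; the article simply states no more efficient rule for its two primary contrasts.

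On the plan's own planning assumption, Holm adds about 5 points of power per arm (80% to 85%) and about 9 points for both arms (69% to 78%), with familywise error at or below 5%. This rests on a two-sided 0.025, equal arm sizes and both arms being effective. If only one arm works, there is practically no gain. Absolute power cannot be checked, because the SD of the 6MST is not given.

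**What to change.** Add to the Data Analysis section, before the 6-month data are analysed, a statement such as: *The two 6MST contrasts with control are tested by the Holm procedure at a two-sided familywise level of 0.05: the smaller p value is compared with 0.025 and, if it is rejected, the other with 0.05.* Hommel is also acceptable, since the shared control makes the two statistics positively correlated; Holm needs no dependence assumption. Keep 0.025 in the Sample Size section as the conservative planning level.

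In the same place, say how this step feeds the gatekeeping families, including how it relates to strength and the stand-up test in the first family. If strict control across families is wanted, either accept that no alpha passes on when only one 6MST contrast is rejected (about 13% at the planned effect) or specify a truncated Holm.

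The cost is a few sentences; no participants, visits or data are needed.

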#### Data Analysis

Primary analyses will use the intention-to-treat approach, considering all included participants in their initial groups and using all data, regardless of the intervention participation level. If protocol deviations are frequent, a per-protocol analysis will be conducted, with a focus on participants who followed the intervention.

The primary outcome analysis will compare scores between groups with modified covariance analysis (ANCOVA), using a linear regression model to analyze postintervention results in relation to the intervention group while accounting for baseline values, age, and sex. Robust linear regression will be used if necessary. A parallel gatekeeping procedure with the following four families of end points will be used to control the type I error risk for secondary end points: (1) the primary family includes the end points related to physical capacity (6MST, strength, and 30-second stand-up test), (2) comorbidities (high blood pressure, high fasting glycemia, obesity, and insulin resistance), (3) disability (HIV Disability Questionnaire scores), (4) mental health (quality of life and Personal Health Questionnaire 9 scores). End points of comorbidities, disability, and mental health families will be analyzed only if at least one primary end point is significant (with the Hommel method used to control for type I error). Secondary end points will be analyzed using the same approach with the ANCOVA model. Exploratory analyses will analyze repeated data using mixed-effects linear models, and Generalized Additive Mixed Model will be used to model nonlinear relationships. Missing data will be described and imputed using multiple imputations by chained equations, assuming that they are randomly missing, with estimates obtained via Rubin’s method.

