**Exclusion criteria**
Medical contraindications to physical activity.Anticipated unavailability.Severe functional limitation (SPPB ≤3).Another health condition requiring priority care.

Recruitment will take place in 2 health centers in the Abobo district, a popular neighborhood on the outskirts of Abidjan. The first center, “Formation Urbaine Sanitaire Abobo Avocatier,” located in eastern Abobo, has an active cohort of approximately 1500 people living with HIV, including 500 individuals aged 50 years and older. The second center, “Centre Médicalisé Spécialisé El Rapha,” has an active cohort of 2000 people living with HIV, including approximately 650 individuals aged 50 years and older. Participants who fulfill the inclusion criteria are contacted by their clinicians, who will obtain their informed consent to participate in the study (Multimedia Appendix 1).

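### Randomisation is stratified by site, but the stated covariates of the primary ANCOVA omit site; if site predicts the outcome, the analysis is mildly conservative

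*Protocol article*

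**What the plan says.** Under Randomization and Blinding, the protocol article allocates participants "Randomization will use fixed-size blocks and be stratified by study site", "in a 1:1:1 ratio into one of three arms". Study Population and Recruitment names two centres: "Recruitment will take place in 2 health centers in the Abobo district". The first "has an active cohort of approximately 1500 people living with HIV, including 500 individuals aged 50 years and older"; the second "has an active cohort of 2000 people living with HIV, including approximately 650 individuals aged 50 years and older".

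Under Data Analysis, the primary model is an ANCOVA, "using a linear regression model to analyze postintervention results in relation to the intervention group" "while accounting for baseline values, age, and sex". The secondary end points follow the same ANCOVA approach. Site is not among the named covariates, and no other section adds it. Robust regression is offered as a fallback, but that does not bring site into the model.

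For the exploratory mixed models and the multiple imputation, the article names methods but no covariates.

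**The concern.** Blocking within site keeps the arms nearly balanced across the two centres, so a difference between centres contributes almost nothing to the variance of the arm comparison. A model without site does not know this. It leaves the between-site variance in the residual and reports a standard error that is larger than the true one. Confidence intervals are then wider and p-values larger than the design warrants, and some of the precision that stratification bought is not used.

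The full protocol or an SAP might add site. But the article states a specific covariate list, and that list omits the only named stratification factor. It is a stated model choice and can be reviewed as one.

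At stake is a small amount of power in a trial sized at exactly 80% for each comparison with control. Recruitment is complete according to the Results section, so precision can now come only from the analysis.

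**Working it through.** **Inputs from the protocol article (Sample Size):** target difference, for which the article says "which translates into a difference of approximately 10 steps"; 50 analysable participants per group; 80% power; type I error 0.025 per comparison, taken here as two-sided because sidedness is not stated.

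**Inputs that are assumptions:** the residual SD, which the article does not give, and R², the share of residual variance that site explains after baseline, age and sex. R² is shown at 2%, 5% and 10%.

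**Step 1. SD implied by the plan's own figure.** With z(0.9875) = 2.2414 and z(0.80) = 0.8416,

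SD = 10 × √(50/2) / (2.2414 + 0.8416) = 50 / 3.0830 = 16.2 steps.

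So 50 per group is consistent with an SD of 16.2. This is a back-solution and not an independent check of the sample size. A one-sided reading of 0.025 would imply about 17.9.

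**Step 2. Reported and true standard errors.**

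- Reported by the model without site: SE_rep = 16.2 × √(2/50) = 3.240.
- True under allocation blocked within site: SE_true = 3.240 × √(1 − R²), which is 3.207, 3.158 and 3.074 at R² of 2%, 5% and 10%.

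**Step 3. Consequences.**

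- Overstatement of the SE: 1/√(1 − R²) − 1
- Actual type I error without site: 2 × [1 − Φ(2.2414/√(1 − R²))]
- Power without site: Φ((10 − 2.2414 × 3.240)/SE_true) = Φ(2.738/SE_true)
- Power with site: Φ(10/SE_true − 2.2414)

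| R² (assumed) | SE overstated by | Actual type I error, nominal 2.5% | Power without site | Power with site | Gain (points) |
|---|---|---|---|---|---|
| 0 | 0 | 2.5% | 80.1% | 80.1% | 0 |
| 2% | 1.0% | 2.4% | 80.3% | 81.0% | 0.6 |
| 5% | 2.6% | 2.1% | 80.7% | 82.3% | 1.6 |
| 10% | 5.4% | 1.8% | 81.3% | 84.4% | 3.1 |

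The first row is 80.1% and not 80.0% because the SD is rounded to 16.2. Gains are taken from unrounded powers. The SE and type I error columns depend on R² alone; only the power columns use the SD.

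**Step 4. What those R² values mean in steps.** If recruitment follows the cohort sizes (500 and 650 aged 50 or older, an assumption), the first site holds p = 500/1150 = 0.435, and p(1 − p) = 0.2457. The adjusted gap between sites is 16.2 × √(R²/0.2457), which is 4.6, 7.3 and 10.3 steps for R² of 2%, 5% and 10%.

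**Step 5. Simulation check.** The set-up was 150 analysed, three arms, blocks of 6 (assumed) within two sites of 66 and 84, and 5000 runs per setting. The ratio of the SE without site to the SE with site was 1.026 at R² = 5% and 1.056 at 10%. Power rose from 78.6% to 80.3% at 5% and from 80.0% to 83.1% at 10%. Levels sit slightly below the formula, which uses normal quantiles and ignores the cost of the covariates, but the gains of 1.7 and 3.2 points agree. The simulated error rates have a Monte Carlo error of about √(0.025 × 0.975/5000) = 0.2 percentage points, so they are too coarse to confirm the smaller shifts in the type I error column.

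**The case against.** The strongest reply is that the loss may be close to nothing. It exists only if site predicts the 6-month step count after the baseline step count, age and sex. Stable differences between centres in staff, test conditions or case mix would also show in the baseline test, which is already in the model. Both centres lie in one district, and the article reports no difference between them. The 10% case needs an adjusted gap of about 10 steps, as large as the effect the trial is sized to detect. All of this stands, and it keeps the point minor.

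A reader might infer four stronger things that the documents do not support:

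- **That the primary result would be biased or the error rate inflated.** Stratified blocking balances the arms across sites, and the error runs towards conservatism.
- **That the trial falls below its planned power.** With total residual SD held at 16.2, power without site stays at or slightly above 80%, because stratification already reduces the true variance of the estimate. For the same reason, setting the with-site power against a flat 80% overstates the gain: at R² = 10% it suggests about 4 points instead of 3.1.
- **That differences between coaches are a reason for a site indicator.** Coaches supervise exercise and controls receive health education, so such differences would act mainly as a site-by-arm effect, which a single site indicator does not model.
- **That the mixed models and the imputation model are also misspecified.** The article gives no covariate list for either, and such detail is commonly left to the full protocol or SAP.

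**Conclusion.** The point holds as a minor, conditional weakness. The stated covariate list for the primary ANCOVA, and for the secondary end points analysed in the same way, omits the factor on which randomisation was stratified. The plausible cost runs from nothing to about 3 points of power for R² up to 10%, with intervals up to about 5% too wide.

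This rests on two assumptions that the documents cannot settle: the share of residual variance due to site, and the residual SD of 16.2 steps. If the residual SD differs, the power levels and gains change, but the SE overstatement and the actual type I error do not. The validity of the primary comparison is not in question.

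**What to change.** Add study site as one fixed indicator to the primary ANCOVA and to the secondary ANCOVAs that follow it. Keep the imputation model consistent by including site there too.

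The statistical cost is one degree of freedom, and site is already recorded for randomisation. The administrative cost is a documented amendment: Ethical Considerations requires the sponsor and scientific committee to validate protocol changes and the ethics committee to be informed. Timing matters, because the Results section puts the start of the 6-month evaluation in November 2025. The change should be recorded before outcome data are examined by arm, so that the added covariate cannot look data-driven. If that moment has passed, the model with site should be reported beside the stated model and labelled as added later.

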### Effectiveness Outcome Assessment

In this type 2 hybrid design, both effectiveness and implementation will be evaluated and receive equal attention. For clarity, effectiveness outcomes are presented in this section, and implementation research is presented in the following section. The primary effectiveness outcome is the difference in the number of steps completed during a 6-minute step-up test (6MST) at 6 months. The 6MST is a submaximal aerobic test that provides information on cardiorespiratory and functional capacities. Although less accurate than maximal exercise tests (with ergocycles or treadmills), the 6MST was selected because it does not require sophisticated technology and is easier to implement in resource-limited settings. Compared with the 6MWT, a reference for submaximal exercise tests [51], the 6MWT has similar good reproducibility and reliability [51,52] but is easier to perform. In addition, it is slightly more demanding, which is appealing for the evaluation of adults with relatively good health. The other effectiveness outcomes included in this study reflect key health outcomes relevant to aging individuals living with HIV and will be measured at 6 and 12 months. These include evaluations of strength, balance, cognitive performance, quality of life, depression, daily autonomy, social participation, blood pressure, and glucose metabolism. Details on the operationalization of all effectiveness outcomes are provided in Multimedia Appendix 2. All effectiveness outcomes will be assessed by investigators blinded to the participants’ assigned intervention arm (single-blind).

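### The 6MST is declared and sized as the single primary outcome, but the Data Analysis section tests it within a three-member primary family, any member of which can open the secondary families

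*Protocol article*

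**What the plan says.** Effectiveness Outcome Assessment names one primary outcome: "The primary effectiveness outcome is the difference in the number of steps completed during a 6-minute step-up test (6MST) at 6 months". The Methods paragraph of the Abstract also names the 6MST alone.

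Sample Size builds on that outcome. The effect is taken from "the 6MST test (115 steps vs 105 steps"), the claim is that "50 participants per group will ensure 80% power to detect a significant difference between the intervention and control groups", and the level is set by "assuming a type I error rate of 0.025 (adjusted for multiple comparisons regarding the primary end point"). End point is singular there, and the same section says that the trial is powered for each intervention arm against control. So 0.025 reads as 0.05 shared between two contrasts.

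Data Analysis first describes an ANCOVA for the primary outcome. It then sets up a parallel gatekeeping procedure, whose stated purpose is type I error control for the secondary end points, with four families. Of these, "the primary family includes the end points related to physical capacity (6MST, strength, and 30-second stand-up test"). Comorbidities, disability and mental health are analysed only if one or more of the primary end points is significant, with Hommel as the method.

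**The concern.** The article uses the term primary end point in two ways. In the outcome and sample-size sections it means the 6MST. In the gatekeeping rule it means any of three measures. Two consequences follow.

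- **Gate.** Strength or the stand-up test can satisfy the rule while the 6MST does not. The report could then cite a significant primary end point and proceed to the secondary families, although the outcome on which the trial was sized showed nothing.
- **Level.** If the 6MST is judged inside the Hommel family, its significance level depends on two other end points. The sample size assumed 0.025 outright, with nothing set aside for them.

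The text does not say whether the 6MST is tested separately or only within the family. The same data could therefore give different verdicts on the primary outcome.

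**Working it through.** **Inputs from Sample Size.** Difference 10 steps (115 minus 105), 50 per group, 80% power, level 0.025. Two inputs are not given and are assumed here: the test is two-sided, and the SD is back-solved.

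**The plan's own figures.** The inflation reproduces: 50 × 1.2 = 60 per arm, and 3 × 60 = 180. The 50 per group cannot be checked without an SD, so I solved for the SD that returns it:

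SD = 10 × √(50/2) / (2.2414 + 0.8416) = 50 / 3.0830 = 16.2 steps.

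By construction, the 6MST tested alone at two-sided 0.025 then has 80% power. If 0.025 were one-sided, the SD would be 17.8 (17.85 before rounding).

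**The 6MST inside a three-member family at 0.025 per contrast.** Under Hommel the 6MST is significant for certain if p ≤ 0.025/3 = 0.0083. It can be significant up to p = 0.025 only if the other two end points are also small enough. At the strictest level:

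power = Φ(3.083 − 2.638) = Φ(0.445) = 67.2% with 50 per arm, or 77.0% if all 60 per arm are evaluable. Reaching 80% at that level needs 64 evaluable per arm.

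For the full procedure I simulated Hommel as closed Simes tests on three correlated normal statistics (correlation 0.3 and 0.5, 50 per arm):

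| Effect on strength and stand-up | Power for 6MST |
|---|---|
| None | 67% |
| Half the standardised effect | 68 to 69% |
| Same standardised effect | 76% |

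**The gate, with the 6MST truly null.** Share of trials in which the family has a significant member but the 6MST is not significant, for one contrast:

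| Effect at the sizing level on | Correlation 0.3 | Correlation 0.5 |
|---|---|---|
| Strength only | 67% | 67% |
| Strength and stand-up | 84% | 81% |

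**Other readings of the same text.**
- One family of six hypotheses (three end points, two contrasts sharing the control arm) under Hommel at 0.05: power for the 6MST per contrast is about 69 to 71% if the other end points have no effect or half the effect, and about 81% if all respond equally.
- The 6MST tested alone at 0.025 per contrast, with Hommel serving only the gate: 80%, unchanged.

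**ANCOVA.** The analysis adjusts for baseline, age and sex; the sample-size text does not mention this. If 16.2 is a raw SD, a correlation r between baseline and 6-month values multiplies the variance by 1 − r². Restoring 80% at 0.0083 requires 1 − r² = (3.083 / 3.480)² = 0.785, so r of about 0.46.

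**The case against.** The strongest reply is that the gatekeeping is said to serve the secondary end points, and that the ANCOVA for the primary outcome is described before it and on its own. Read that way, the 6MST is tested at 0.025 per contrast and Hommel decides only whether families 2 to 4 are analysed. This is a fair reading, and under it the power is untouched. A reader might infer from the three-member family that the stated 80% is not delivered. The documents do not support that as a flat statement: it follows from one reading only, and its size rests on an SD, a sidedness and correlations that are not given. A six-hypothesis family with all end points responding shows no loss, and ANCOVA precision could offset one.

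The second reply is that parallel gatekeeping is meant to open on any member of the first family, and that opening the gate does not declare the 6MST positive. Both statements are true, and I do not claim that opening on any member is in itself a type I error fault. How the contrasts share alpha, and how alpha passes between families, may be set out in fuller documents that are not shown.

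What neither reply removes is the contradiction. The article itself calls all three measures primary end points for the rule that opens the gate, after naming and sizing only one. A fuller plan would have to overrule one of these statements. That the trial calls itself a pilot does not change this, since it still claims 80% power for a confirmatory comparison with control.

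**Conclusion.** The point holds as a contradiction in a stated decision rule. One primary outcome is named and powered, three are treated as primary in the gatekeeping, and the gate can open on strength or chair stands with a non-significant 6MST. On the sizing effect this would occur in about 67% of trials if only strength responds and in 81 to 84% if both do. These figures are for one contrast, a truly null 6MST, 50 per arm, correlation 0.3 to 0.5, and Hommel at 0.025 per contrast.

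The effect on power is conditional. It is about 67 to 76% instead of 80% if the 6MST is judged by its Hommel-adjusted result at 0.025 per contrast, with SD 16.2 back-solved from a two-sided 0.025 and no credit for ANCOVA. There is no loss if the 6MST is tested alone.

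**What to change.** State in Data Analysis that the 6MST at 6 months is tested alone in the two contrasts with control, each at 0.025 or by Holm or Hommel at 0.05 across the two. Move strength and the 30-second stand-up test to the first secondary family. Let only a significant 6MST open the gate.

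If the three-member primary family is wanted instead, declare all three as primary end points throughout, say how the two contrasts enter the family, and restate the power for the Hommel procedure with the SD and correlations it assumes.

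The cost is wording, provided that it is settled and dated before the 6-month data are analysed by arm. The Results section reports that all participants are randomised, so a larger sample is no longer a practical remedy. The downside of the first option is that strength and stand-up could no longer open the gate, so a benefit confined to them would be reported without formal testing of the later families.
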